# Effect of various dialysis modalities on intradialytic hemodynamics, tissue injury and patient discomfort in chronic dialysis patients: design of a randomized cross-over study (HOLLANT)

**DOI:** 10.1186/s12882-021-02331-z

**Published:** 2021-04-15

**Keywords:** Hemodialysis, Hemodiafiltration, Intradialytic blood pressure, Intradialytic tissue injury, Intradialytic patient tolerance, Multicentre randomized controlled cross-over trial

## Abstract

**Background:**

From a recent meta-analysis it appeared that online post-dilution hemodiafiltration (HDF), especially with a high convection volume (HV-HDF), is associated with superior overall and cardiovascular survival, if compared to standard hemodialysis (HD). The mechanism(s) behind this effect, however, is (are) still unclear. In this respect, a lower incidence of intradialytic hypotension (IDH), and hence less tissue injury, may play a role. To address these items, the HOLLANT study was designed.

**Methods:**

HOLLANT is a Dutch multicentre randomized controlled cross-over trial. In total, 40 prevalent dialysis patients will be included and, after a run-in phase, exposed to standard HD, HD with cooled dialysate, low-volume HDF and high-volume HDF (Dialog iQ® machine) in a randomized fashion. The primary endpoint is an intradialytic nadir in systolic blood pressure (SBP) of < 90 and < 100 mmHg for patients with predialysis SBP < 159 and ≥ 160 mmHg, respectively. The main secondary outcomes are 1) intradialytic left ventricle (LV) chamber quantification and deformation, 2) intradialytic hemodynamic profile of SBP, diastolic blood pressure (DBP), mean arterial pressure (MAP) and pulse pressure (PP), 3) organ and tissue damage, such as the release of specific cellular components, and 4) patient reported symptoms and thermal perceptions during each modality.

**Discussion:**

The current trial is primarily designed to test the hypothesis that a lower incidence of intradialytic hypotension contributes to the superior survival of (HV)-HDF. A secondary objective of this investigation is the question whether changes in the intradialytic blood pressure profile correlate with organ dysfunction and tissue damage, and/or patient discomfort.

**Trial registration:**

Registered Report Identifier: NCT03249532# (ClinicalTrials.gov). Date of registration: 2017/08/15.

## Background

Despite the use of high permeable dialyzers, which combine diffusive with convective transport, the clinical outcome of hemodialysis (HD) patients remains poor. In online post-dilution hemodiafiltration (HDF), diffusion is by and large similar to HD, while the amount of convective transport is considerable higher. Recently, four randomized controlled trials (RCT) have been published which compared HD with HDF [1–4]. Although the results of the individual studies were inconclusive, a recent meta-analysis on individual participant data (IPD) showed a superior outcome for patients treated with HDF (all-cause mortality HR 0.86 [95% CI: 0.75; 0.99]). The largest mortality reduction was obtained in patients receiving the highest convection volume (high-volume HDF [HV-HDF] > 23 L/1.73 m^2^/session: all-cause mortality HR 0.78 [95% CI: 0.62; 0.98], if compared to HD) [5].

Nonetheless, it is still unclear why HV-HDF is associated with an improved survival [6]. On theoretical grounds, both the enhanced removal of middle molecular weight uremic retention products and a superior bio-incompatibility (BI) profile [7], including less inflammation [8, 9] and less dialysis-induced hypoxia [10, 11], may play an important role. Moreover, since treatment with HDF has been associated with a lower incidence of intradialytic hypotension (IDH) than standard HD [12–15], in which an altered sodium removal during HDF may play a role [16], a lesser amount of dialysis-induced tissue damage may also contribute to the beneficial effect of HDF on survival.

Since IDH is a frequently occurring side-effect of HD treatment and microcirculatory dysfunction is a prominent feature of patients with advanced chronic kidney disease (CKD) [17, 18], every single dialysis session may further deteriorate the already affected structure and function of vital organs, such as the brain, gut and heart [19]. After all, HD-associated cardiomyopathy may result not only from the various inflammatory and metabolic derangements of pre-dialysis CKD [20], but also from HD-induced perfusion deficits [21–27], which is considered a model of repetitive organ ischemia-reperfusion injury. In this respect it is interesting to note that an absolute intradialytic nadir of SBP < 90 and < 100 mmHg for patients with a predialysis SBP < 159 and ≥ 160 mmHg, respectively, appeared most strongly associated with mortality in a large study, comparing the relation between various definitions of IDH and outcome [28]. Considering the gut, HD-induced hypoperfusion may cause disruption of the intestinal barrier and permit the translocation of gut-derived endotoxins, bacterial DNA and/or intact bacteria into the blood. Circulating bacterial fragments may contribute to systemic inflammation, cardiovascular disease, and reduced survival in these patients [29–34].

As intradialytic blood pressure measurements were not the primary endpoint in any of the above-mentioned studies in HDF patients [12–15], it is still unclear if, and if so, *why* this modality is associated with less IDH than standard HD (S-HD). Since IDH can be alleviated by HD treatment with cooled dialysate (C-HD) and (HV-) HDF may induce cooling of the extracorporeal circuit and subsequent cooling of the patient‚ thermal factors may play an important role in this respect [12–15, 35–44] and are even considered to be exclusively responsible for the superior outcome of HDF treatment [45]. Yet, despite the physical benefits of a reduction in IDH and related symptoms, patients may suffer from shivering and cold (sensations). Interestingly, from a large recent RCT it appeared that intradialytic patient tolerance was significantly better during HDF, if compared to treatment with S-HD [3]. As of yet, however, it is unknown which intermittent extracorporeal renal replacement therapy (S-HD, C-HD, LV-HDF or HV-HDF) has the most favorable intradialytic patient tolerance profile. Altogether, current data suggests that (HV)-HDF is the preferred treatment to circumvent dialysis-induced IDH, and hence, to alleviate the repetitive microcirculatory dysfunction and subsequent tissue damage of dialysis treatment. So far, however, comparative data between S-HD, C-HD, LV-HDF and HV-HDF are lacking.

Therefore, the protocol for the current investigation with the original title “Effect of high-volume Online hemodiafiLtration on intradiaLytic hemodynamic (iN)sTability and cardiac function in chronic hemodialysis patients” (HOLLANT) was designed. In this randomized cross-over clinical study, not only intradialytic hemodynamics will be investigated, but also changes in cardiac performance and signs of myocardial injury. In addition, besides markers of inflammation and oxidative stress, intradialytic tissue damage, as indicated by various cell surface markers and the transfer of microbial DNA (mDNA) from the gut to the blood, will be investigated. Hence, finally, since cool dialysate may induce cold (sensations) and shivering [37], patient tolerance and thermal perception will be compared between the four modalities.

### Objectives

The primary objective of the HOLLANT study is to evaluate whether intradialytic hemodynamic stability is better preserved during HV-HDF, by comparing the frequency of intradialytic hypotensive episodes between S-HD, C-HD, LV-HDF and HV-HDF. The main secondary objectives include intradialytic signs of tissue damage as measured by Speckle Tracking Echocardiography (STE), a diversity of laboratory parameters, and patient reported outcome measures (PROMs), such as tolerance and cold (sensations).

## Methods

### Study design

The HOLLANT study is an open, cross-over, multicenter, intervention RCT in chronic intermittent dialysis patients who will be exposed to four different dialysis modalities: 1) S-HD: HD with a dialysate temperature of 36.5 °C. 2) C-HD: HD with a dialysate temperature 35.5 °C. 3) LV-HDF: HDF with a convection volume of 15 L/1.73 m^2^/session and a dialysate temperature of 36.5 °C. 4) HV-HDF: HDF with a convection volume of ≥23 L/1.73 m^2^/session and a dialysate temperature of 36.5 °C.

After enrollment, participants will be randomized centrally to the four dialysis modalities by using computer randomization software [46]. Randomization occurs in blocks. Enrolled patients will be treated with their usual dialysis modality (either HD or HDF) during the first 2 weeks of the study. Patients who cannot achieve or tolerate a blood flow rate ≥ 350 mL/min during this run-in phase will be excluded before the actual start of the study. Treatment times will be fixed at 4 h per session during the entire conduct of the study. Thereafter, patients start the study-phase and will be treated with S-HD, C-HD, LV-HDF or HV-HDF in a random order. Each dialysis modality will last 2 weeks. The total study duration is 2 (run-in phase) + 8 (study phase) = 10 weeks per patient. An overview of the study is shown in Fig. 1.

**Fig. 1 Fig1:**

Overview of study scheme. The run-in phase during week − 1 and week 0 (total duration of 2 weeks) is followed by the four different dialysis treatment modalities (S-HD, C-HD, LV-HDF, HV-HDF) in a randomized order (total duration of 8 weeks).  = Non-invasive advanced hemodynamic monitoring (Clearsight) during the first or second treatment of the last week and measurement of blood pressure every 15 min;  = assessment of STE, blood sampling and measurement of blood pressure every 15 min;  = measurement of blood pressure every 30 min

### Study population

We plan to include 40 patients. For reasoning (see “Sample size considerations” below), patients will be recruited from three dialysis facilities: a commercial dialysis clinic (Niercentrum aan de Amstel, Amstelveen, The Netherlands), a large community based clinical hospital (St. Antonius Hospital, Nieuwegein, The Netherlands) and a university hospital (Amsterdam UMC, location VU University Medical Center, Amsterdam, The Netherlands). The in- and exclusion criteria are depicted in Table 1. Severe incompliance to the dialysis procedure and accompanying prescriptions is defined as non-adherence to the dialysis prescription.

**Table 1 Tab1:** Inclusion and exclusion criteria

**Inclusion criteria**	
- Patients treated with HD or HDF 3 x per week during at least 4 h for at least 2 months.	
- Ability to understand study procedures.	
- Willingness to provide informed consent.	
- Dialysis single-pool Kt/V for urea (spKt/Vurea) ≥ 1.2^a^	
- Achievement of a blood flow of ≥350 ml/min and/or convection volume of ≥23 Liter per treatment during the run-in phase.	
- Dialysis access recirculation < 10%^a^.	
**Exclusion criteria**	
- Age < 18 years.	
- Life expectancy < 3 months.	
- Participation in another clinical intervention trial.	
- Severe incompliance to the dialysis procedure and accompanying prescriptions.	

^a^Based on the most recent (before start of the study) measurements from daily practice, in accordance with the applicable national and international guidelines [47, 48]

### Dialysis prescription and equipment

#### Dialysis modalities

HDF will be performed in the post-dilution mode with a target convection volume (substitution volume + net ultrafiltration [UF] volume) of 15 L (LV-HDF) or 25 L (≥23 L, HV-HDF). Extracorporeal blood flow rate will be targeted at 350–400 ml/min and filtration fraction (blood flow rate / convection flow rate) at 25–30%, which have been proven to be feasible [49]. Substitution fluid is prepared from the dialysis fluid by one additional step of UF with a dialysis fluid filter (Diacap® Ultra, B. Braun Avitum AG, Melsungen, Germany), before it is infused into the blood after the dialyzer. The electrolyte composition of the substitution fluid is identical to the electrolyte composition of the dialysate.

For a given patient, treatment settings will be kept similar in all treatment modalities, e.g. UF profile, start of treatment with either empty or filled lines, blood flow rate, session length and type of anticoagulant. Any clinically necessary change will be documented.

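### The 25–30% filtration-fraction target is not limited to one HDF arm and cannot hold with 15 L in 4 h at 350–400 mL/min; its printed ratio is also inverted

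*Protocol article*

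**What the plan says.** All of this is in the Methods of the protocol article.

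- **Study design** defines the two HDF arms by convection volume, indexed to body surface area: "LV-HDF: HDF with a convection volume of 15 L/1.73 m^2^/session" and "HV-HDF: HDF with a convection volume of ≥23 L/1.73 m^2^/session". It also fixes session length: "Treatment times will be fixed at 4 h per session during the entire conduct of the study".
- **Dialysis modalities** gives the "target convection volume (substitution volume + net ultrafiltration [UF] volume") as "of 15 L (LV-HDF) or 25 L (≥23 L, HV-HDF"), here in litres without indexing. The next sentence covers HDF without naming an arm: "Extracorporeal blood flow rate will be targeted at 350–400 ml/min", together with "filtration fraction (blood flow rate / convection flow rate) at 25–30%, which have been proven to be feasible".
- The same section says that, for a given patient, "treatment settings will be kept similar in all treatment modalities, e.g. UF profile"; its list of examples goes on to include blood flow rate and session length.
- **Dialysis-related recordings** has the achieved convection volume noted after every HDF session, in L/session.

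No section gives a separate filtration fraction for LV-HDF.

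**The concern.** Four settings are stated for LV-HDF: volume, session length, blood flow and filtration fraction. Any three determine the fourth, so they must agree. They do not, and the formula given for the filtration fraction has its numerator and denominator exchanged.

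Convection volume is the only stated difference between LV-HDF and HV-HDF, and the Discussion names LV-HDF as one of the three modalities against which HV-HDF is to be compared. A site that set LV-HDF by filtration fraction would narrow or remove that contrast. A site that lowered blood flow or shortened the session to satisfy both 15 L and 25–30% would depart from the rule of similar settings and mix the volume effect with blood flow or time. With three centres, the text leaves room for different resolutions.

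**Working it through.** **Inputs.** Volumes of 15 L, 25 L and the 23 L floor, blood flow 350–400 mL/min, and filtration fraction (FF) 25–30% (Dialysis modalities); session 4 h = 240 min (Study design). Convection volume already includes net ultrafiltration, so no further term has to be added.

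**Step 1: FF implied by each volume.** FF = (volume / 240 min) / blood flow.

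| Volume | Convection flow | FF at 350 mL/min | FF at 400 mL/min |
|---|---|---|---|
| 15 L (LV-HDF) | 62.5 mL/min | 17.9% | 15.6% |
| 23 L (HV-HDF floor) | 95.8 mL/min | 27.4% | 24.0% |
| 25 L (HV-HDF target) | 104.2 mL/min | 29.8% | 26.0% |

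The stated 25–30% is reproduced for 25 L. It is not reproduced for 15 L anywhere in the blood flow range.

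**Step 2: volume implied by the FF target.** Volume = blood flow × FF × 240 / 1000.

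- 350 × 0.25 × 0.240 = 21.0 L; 350 × 0.30 × 0.240 = 25.2 L
- 400 × 0.25 × 0.240 = 24.0 L; 400 × 0.30 × 0.240 = 28.8 L

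Against 15 L, the excess is 21.0/15 − 1 = 40% to 28.8/15 − 1 = 92%. Of the rectangle spanned by 350–400 mL/min and 25–30%, the part with blood flow × FF below 95.8 mL/min gives less than 23 L. That part is 15.4% of the area, so about 85% is at or above 23 L. This is a share of the stated target range, not a forecast of sessions.

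**Step 3: what would have to give way to keep both 15 L and 25–30%.**

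- Blood flow: 62.5/0.30 = 208 to 62.5/0.25 = 250 mL/min. Study design excludes patients who cannot reach 350 mL/min.
- Time: 15 000/(400 × 0.30) = 125 min to 15 000/(350 × 0.25) = 171 min. The stated time is 240 min.

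**Step 4: body surface area (BSA).** Steps 1–3 use absolute litres, which equals the indexed definition only at 1.73 m². The article gives no BSA, so the values below are assumptions. The indexed LV-HDF target is 15 × BSA/1.73.

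| Assumed BSA | LV-HDF target | LV-HDF FF (400 to 350 mL/min) | Excess if 25–30% is followed | Share of rectangle ≥ 23 L/1.73 m² |
|---|---|---|---|---|
| 1.6 m² | 13.9 L | 14.5–16.5% | 51–108% | over 99% |
| 1.73 m² | 15.0 L | 15.6–17.9% | 40–92% | 85% |
| 1.8 m² | 15.6 L | 16.3–18.6% | 35–84% | 67% |
| 1.9 m² | 16.5 L | 17.2–19.6% | 28–75% | 38% |
| 2.0 m² | 17.3 L | 18.1–20.6% | 21–66% | 15% |

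LV-HDF reaches 25% at 350 mL/min only if BSA is at least 21.0/15 × 1.73 = 2.42 m².

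**Step 5: the printed ratio.** Blood flow / convection flow is 350/62.5 = 560% to 400/62.5 = 640% for 15 L, and 350/104.2 = 336% to 400/104.2 = 384% for 25 L. For that ratio to be 25–30%, convection flow would have to be 350/0.30 = 1167 to 400/0.25 = 1600 mL/min, or 280–384 L in 240 min.

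**The case against.** The strongest reply is that convection volume defines the arms and filtration fraction is only an operating setting. Study design separates LV-HDF from HV-HDF by volume alone, and Dialysis modalities opens with the volume targets. Since 25 L gives almost exactly the stated range, the natural reading is that 25–30% describes how the high volume is reached. Staff who follow 15 L keep the arms apart. Lowering blood flow or shortening sessions is already ruled out by the text, achieved volume is recorded at every session, and a necessary change of settings is to be documented. Nobody could act on the inverted ratio.

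Most of this stands. A reader might infer that LV-HDF as planned turns into HV-HDF, or that the contrast has already been lost in the patients treated so far. The document supports neither. It does not show that any site sets LV-HDF by filtration fraction. Even if one did, about 15% of the stated range lies below 23 L at 1.73 m², and at 2.0 m² about 85% lies below the indexed floor. The 40–92% excess is likewise one case, tied to absolute litres, and not a general figure.

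The reply does not remove the inconsistency. The sentence follows directly on both volumes and names no arm, so the restriction to HV-HDF is the reader's inference. Nor is this a detail left to a fuller protocol: the article itself states settings that cannot hold together. Indexing to BSA does not rescue them at any of the assumed body sizes shown.

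**Conclusion.** The point holds as an inconsistency in the stated treatment settings. With 4 h and 350–400 mL/min, 15 L corresponds to a filtration fraction of 15.6–17.9% (18–21% at an assumed BSA of 2.0 m²), outside the 25–30% that the text applies to HDF without restriction. The ratio is printed upside down.

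The consequence is conditional. If the filtration fraction governed, LV-HDF would receive 21.0–28.8 L: 40–92% above target in absolute litres, about 21–66% at 2.0 m², with an overlap with HV-HDF that is large at 1.73 m² and shrinks as BSA rises. If the volume governed, the arms would remain separate and only the filtration-fraction target would be missed. The document does not say which governs, and this review takes no position on which setting is right. The arithmetic rests only on printed figures; BSA is the one assumption.

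**What to change.** 1. Reconcile Study design with Dialysis modalities so that volume, blood flow, session length and filtration fraction agree for each HDF arm.
2. State to which arm or arms the 25–30% range applies, and which target has priority when they conflict. That choice is the sponsor's; it should be the same in all three centres.
3. Correct the ratio to convection flow divided by blood flow.
4. State whether the volume targets are absolute or per 1.73 m². Study design indexes them; Table 1, Dialysis modalities and Dialysis-related recordings use plain litres.
5. Report achieved convection volume by arm and centre, including for the 25 patients already enrolled according to Trial status, so that the LV-HDF versus HV-HDF contrast can be verified.

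The cost is a wording correction, a note to the sites and one table. The achieved volumes are already recorded after each HDF session; if the targets are meant to be indexed, BSA is needed as well, which the echocardiography section already uses for indexing.

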#### Dialyzers

Both HD and HDF will be performed with high-flux dialyzers: Xevonta® 23 dialyzers (membrane material: Amembris, i.e. polysulfon-based membrane with polyvinylpyrrolidone; UF coefficient: 124 ml/min/mmHg; surface area 2.3 m^2^; sterilization by gamma radiation; capillary internal diameter 195 μm; B. Braun Avitum AG, Melsungen, Germany). In exceptional cases, the attending nephrologist can decide to treat the patient with a Xevonta® 18 dialyzer (membrane material: Amembris, UF coefficient 99 ml/min/mmHg; surface area 1.8 m^2^; sterilization by gamma radiation; capillary internal diameter 195 μm; B. Braun, Avitum AG, Melsungen, Germany), or comparable.

#### Dialysis machines

All dialysis treatments will be performed on the Dialog iQ® dialysis machine equipped with Adimea®, automatic blood pressure monitor (ABPM), Hematocrit (HCT) sensor with integrated oxygen saturation (spO2) monitoring device, mantled with the captive tubing system DiaStream® iQ (all B. Braun Avitum AG, Melsungen, Germany).

#### Dialysis fluids

All treatments will be performed with ultrapure (UP) dialysis fluids (< 0.1 CFU [colony forming units]/ml, < 0.03 EU [endotoxin units]/ml). Dialysate flow rate will be 500 mL/min during S-HD and C-HD, and 600 ml/min in LV- and HV-HDF (as the substitution fluid is derived from the dialysate flow, the dialysis machine automatically increases the dialysate flow during online HDF). The electrolyte composition of the dialysis fluid is: Na 138–140 mmol/L; K 2.0–3.0 mmol/L; HCO3 30–35 mmol/L; Ca 1.25–1.75 mmol/L; Mg 0.5 mmol/L; Cl 108–109.5 mmol/L; glucose 5.6 mmol/L; acetate 3 mmol/L and will not be changed for each individual patient during the conduct of the study.

### Patient care

Routine patient care is performed according to current national [47] and international [48] quality of care guidelines, including the measurement of single-pool Kt/V for urea (spKt/Vurea) and access recirculation. As in daily clinical practice, dry-weight is assessed weekly by the attending nephrologist by evaluating clinical symptoms, edema and blood pressure before, during and after dialysis. All patients will be administered their usual dose of low molecular weight heparin (LMWH) anticoagulation (i.e. nadroparin or dalteparin). No sodium profiling will be applied and the conductivity of the dialysis fluid will be recorded continuously by the Dialog iQ dialysis machine during the conduct of the study. When a symptomatic IDH occurs during treatment with a dialysate temperature (Td) of 36.5 °C and there is no reaction to fluid administration, Td will be lowered by 0.5–1.0 °C according to standard protocol and noted on patients’ individual record list.

### Data collection

Table 2 provides an overview of the data that will be collected during the study.

**Table 2 Tab2:** Overview of collected variables

*Hemodynamic parameters*	Intradialytic SBP, DBP, MAP, PP, HR, IDH events, Clearsight measurements
*Markers of cardiac damage*	CK-MB, EVs, intradialytic speckle tracking echocardiography
*Markers of endothelial damage*	sv-ICAM-1, EVs
*Markers of gut ischemia*	mDNA, sCD14
*Markers of inflammation*	hs-CRP, IL-6R, EVs
*Special biomarkers*	FGF23 C-term, EVs
*Patient tolerance*	DSI, VAS-TP
*Others*	pO2 from the arterial line, SaO2, body temperature

#### Baseline data registration

At baseline, all relevant information will be documented: i.e. demographical data, information on cardiovascular disease (CVD), cause of renal failure, time on dialysis, co-morbidity, medical history and medication. A history of CVD is defined as a confirmative answer on any of the questions regarding a previous acute myocardial infarction, coronary artery bypass graft, percutaneous transluminal coronary angioplasty, angina pectoris, stroke, transient ischemic attack, intermittent claudication, amputation, percutaneous transluminal angioplasty, peripheral bypass surgery, and renal percutaneous transluminal angioplasty.

